## Abstract

**Background:**

Military field exercises are characterised by high volumes of exercise and prolonged periods of load carriage. Exercise can decrease circulating serum calcium and increase parathyroid hormone and bone resorption. These disturbances to calcium and bone metabolism can be attenuated with calcium supplementation immediately before exercise. This randomised crossover trial will investigate the effect of calcium supplementation on calcium and bone metabolism, and bone mineral balance, during load carriage exercise in women.

**Methods:**

Thirty women (eumenorrheic or using the combined oral contraceptive pill, intrauterine system, or intrauterine device) will complete two experimental testing sessions either with, or without, a calcium supplement (1000 mg). Each experimental testing session will involve one 120 min session of load carriage exercise carrying 20 kg. Venous blood samples will be taken and analysed for biochemical markers of bone resorption and formation, calcium metabolism, and endocrine function. Urine will be collected pre- and post-load carriage to measure calcium isotopes for the calculation of bone calcium balance.

**Discussion:**

The results from this study will help identify whether supplementing women with calcium during load carriage is protective of bone and calcium homeostasis.

**Trial registration:**

NCT04823156 (clinicaltrials.gov).

## Background

Military training is physically arduous [1] and involves prolonged periods of heavy load carriage [2]. The demands of military training [1] and load carriage [2] are greater in women than men, and women have a greater incidence of stress fracture [3]. These sex differences are predominantly due to the typically lower average aerobic fitness, strength, and muscle mass of women than men when completing the same tasks [1–3]. To maintain calcium homeostasis, blood calcium concentrations are tightly regulated [4]. Strenuous exercise disturbs calcium homeostasis; a reduction in serum calcium increases parathyroid hormone (PTH) and markers of bone resorption to maintain circulating concentrations of calcium [5–7]. Exercise intensity and duration influence the magnitude of the exercise-induced disturbance to calcium homeostasis [8]. In young women, load carriage exercise decreased serum ionized calcium, increased PTH, and increased fractional calcium absorption [9]. Calcium supplementation before exercise can mitigate the exercise-induced disturbances to calcium homeostasis, as shown in a series of walking and cycling studies [8]. Military training and field exercise place significant mechanical and metabolic demands on the skeleton [10–14], and the decrease in bone mineral density (BMD) in the axial skeleton and increase in BMD in the appendicular skeleton [15, 16] may be indicative of disturbed calcium homeostasis and/or insufficient calcium intake. A daily calcium supplement (2000 mg·d^− 1^) during military training prevented an increase in PTH [17], augmented tibial adaptations [5, 7], and reduced the incidence of stress fractures [18]. However, the effect of calcium supplementation before an acute bout of military load carriage on calcium and bone metabolism in women is unknown.

Biochemical markers of bone resorption and formation are inherently variable and only infer the metabolic state of bone turnover at the precise instance at which they are measured. Biochemical markers of bone resorption and formation often increase or decrease together and cannot be used to determine overall net bone mineral balance (*i.e.* whether bone resorption or bone formation is the prevailing process) [19]. Skulan and DePaolo (1999) [20] were the first to outline a conceptual model describing the fractionation of calcium isotopes between soft tissue and bone. Differences in isotopic composition between soft tissue and bone were reported, with bone being enriched with isotopically lighter calcium isotopes compared to soft tissue [20, 21]. Decreased BMD is associated with a net loss of calcium from the bone. Using the model formulated by Skulan and DePaolo (1999) [20], measuring changes in the natural calcium isotopic composition of calcium in the urine provides a non-invasive method to determine calcium homeostasis and calcium flux to, and from, bone [22–25]. Six, naturally occurring, stable calcium isotopes exist in the diet: ^40^Ca, ^42^Ca, ^43^Ca, ^44^Ca, ^46^Ca, and ^48^Ca. Bone formation favours the uptake of isotopically lighter calcium isotopes causing a shift in urine composition towards an isotopically heavier state [26]. When bone resorption is dominant, and calcium is lost from bone, the isotopic calcium composition of the urine becomes lighter [27]. Low calcium intake results in a negative bone calcium balance (*i.e.* calcium is derived from the skeleton to maintain serum calcium concentrations) [28], but the effects of military load carriage and calcium supplementation on bone calcium balance, determined from circulating and urinary calcium isotopes, is unknown.

This study will investigate the effect of calcium supplementation on calcium and bone metabolism in response to load carriage exercise (standard military fitness test; 2 h, 20 kg, 6.4 km·h^− 1^) in military women, a population at increased risk of stress fracture during military training compared with men [3]. It is hypothesised that calcium supplementation will attenuate the decline in serum ionized calcium and increase in PTH and bone resorption, and prevent a negative calcium balance during load carriage. A secondary aim will investigate the effect of load carriage on quadricep and hamstring strength. It is hypothesised that quadricep and hamstring strength will be lower following load carriage.

## Methods

This study is a non-blinded randomised crossover controlled trial. Following the completion of a screening visit to confirm study eligibility (Pre-Screening; visit 1), each participant will complete a single load carriage exercise session on two separate occasions (visits 2 and 3) completed in a randomised order; one with a calcium supplement (Supplement) (1000 mg) and one without (Control) (Fig. 1). Block randomisation using a block size of 2 will be performed and there will be no allocation concealment. All laboratory testing will be completed at the Army Human Performance Laboratory based at the Royal Military Academy, Sandhurst, UK.

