### Participants

Thirty women will complete this randomised controlled crossover trial. Participants will: be aged 18 to 36 years old; have a maximal rate of oxygen uptake ($$\dot V$$O_2max_) of ≥ 35 mL·kg^−1^·min^−1^; will be eumenorrhoeic or using the combined oral contraceptive pill, an intrauterine system, or intrauterine device; be weight stable, defined as no change in self-reported body mass ≥ 5% over the previous 3 months; have a BMI between 18 and 30 kg·m^−2^, and; not be pregnant or lactating. Women will be excluded if they: have disordered eating, defined as ≥ 20 on the Eating Attitudes Test – 26 item (EAT-26); are vitamin D deficient, defined as a total 25-hydroxyvitamin D (25(OH)D) < 30 nmol·L^−1^; have a total areal BMD T-score of < − 1; are oligomenorrhoeic or amenorrhoeic (< 9 menstrual cycles in previous 12 months); self-report as currently smoke or vape or have stopped smoking within the previous three months; are taking any medication known to affect bone or calcium metabolism (*e.g.* treatment for thyroid disorders); have a history of heart, liver, or kidney disease, diabetes, or thyroid disorder; have had a stress fracture or other bone injury in the previous 12 months, or; are anaemic (haemoglobin < 12 g·dL^−1^).

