### Pre-screening

Consent to participate will be obtained from all volunteers by the investigators. Participants will have the option to consent for any remaining samples to be retained for follow-up analyses related to calcium metabolism, bone health, and endocrine function.

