### Data analyses

Data management will be conducted by the investigators. All data will be pseudo anonymised, and double data entry and value range checks will be performed. The investigators will collect and assess the outcome measurements. Exercise energy expenditure measured with raw accelerometery data [33] during periods of purposeful exercise, and recorded in the exercise diary, will be processed with the GENEAread R package from CRAN [39] using a cusomized, openly available script [33, 40]. The ratio of ^44^Ca to ^42^Ca (^44^Ca:^42^Ca) in urine, blood and sweat will be measured following published standard procedures [24, 25]. The calcium isotopic composition is reported as δ^44/42^Ca in parts per thousand (‰):

$$\begin{array}{l}{\delta ^{44/42}}Ca{\rm{ }}\left( {{\% _0}} \right){\rm{ }} = {\rm{ }}\\\left[ {{{\left( {^{44}Ca{/^{42}}Ca} \right)}_{Sample}}/{{\left( {^{44}Ca{/^{42}}Ca} \right)}_{Reference}}} \right]{\rm{ - }}1\end{array}$$

Change between pre- and post-load carriage urine samples will be calculated for each load carriage session.

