### Statistical analyses

No previous studies have been published investigating calcium balance through natural calcium isotope ratios in response to exercise or calcium supplementation, therefore the required sample size for this study is calculated based upon data from high and low calcium diets to reflect the Control (no calcium) and Supplement (1000 mg calcium) conditions within this study. The required sample size was calculated in R (version 4.1.1) using the *‘pwr’* package based on testing the null hypothesis that there will be no difference in calcium balance between Control and Supplement conditions. Based on differences in calcium balance between women on a high (~ 1500 mg·d^− 1^) and low (~ 300 mg·d^− 1^) calcium diet (108.6 ± 127.9 vs. − 95.2 ± 24.6 mg·d^− 1^, d = 2.21) [28], and men on a low (376 mg·d^− 1^) and moderate (857 mg·d^− 1^) calcium diet (10.0 ± 6.0 vs. 0.1 ± 1.8 parts per ten thousand, d = 2.24) [22], it is anticipated that 5 people per group will be required to detect a difference in calcium balance between the Control group and Supplement group with an α of 0.05 and a 1 – ß of 0.90. The data from these trials were using chronic diets rather than acute supplementation and so we anticipate that the effect we will see will be much smaller. Therefore, a second sample size calculation was performed from PTH concentration (a secondary outcome) in response to exercise. Based on a 18.86 to 26.83 pg·mL^− 1^ [41–43] higher serum PTH during exercise without calcium supplementation compared with calcium supplementation (following a calcium meal [1352 ± 53 vs. 46 ± 7 mg [42]] or calcium drink [1000 mg·L^− 1^ [41]; 486 mg·L^− 1^ [43]), it is anticipated that 26 people will be required to detect a difference in serum PTH concentration (d = 0.667) between the Control group and Supplement group with an α of 0.05 and a 1 – ß of 0.90. A total sample of 30 will allow us to detect an effect of d ≥ 0.75 with an α of 0.01 and a 1 – ß of 0.90.

A per-protocol analysis will be performed. Significance will be accepted as p < 0.05.

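### Blocks of 2 without concealment in an open crossover make at least 15 of the 30 orders predictable; the risk of bias is modest and conditional, and concealing the order is cheap

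*Protocol article*

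**What the plan says.** The opening paragraph of Methods in the protocol article fixes three features. The trial is open: "This study is a non-blinded randomised crossover controlled trial". What is randomised is the order in which each woman does her Supplement and Control sessions over visits 2 and 3. On how that is done: "Block randomisation using a block size of 2 will be performed and there will be no allocation concealment".

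Other sections supply the setting:

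- Participants: "Thirty women will complete this randomised controlled crossover trial".
- Methods: "All laboratory testing will be completed at the Army Human Performance Laboratory". No stratification is mentioned.
- Pre-screening: "Consent to participate will be obtained from all volunteers by the investigators".
- Data analyses: "The investigators will collect and assess the outcome measurements".
- Statistical analyses: "A per-protocol analysis will be performed".

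The primary analysis is an ANCOVA comparing conditions with the pre-exercise value as covariate. The secondary models have time and condition as fixed effects and participant as a random effect. Neither description names a period or sequence term.

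**The concern.** Random order protects a crossover only if nobody can match the order to the woman. Here the article does not leave concealment to a fuller document; it says that there is none. The block size is also the smallest possible, so in an open trial each odd-numbered allocation reveals the next one. The investigators who take consent also run the sessions, and some sessions must be scheduled around menses or pill breaks while others can take place at any time. That leaves ordinary discretion over who takes the next slot.

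What is at stake is the comparability of the two order groups. If women who adapt differently between a first and a second load carriage are channelled into different orders, that difference enters the Supplement-minus-Control contrast. Adding a period term to the model would not remove it.

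**Working it through.** **Inputs.** 30 women, fixed blocks of 2, open, not concealed (Methods; Participants). One unstratified sequence is assumed, since there is one laboratory and no stratification is stated. The article gives no figure for predictability, so there is none to reproduce. Its sample-size figures do not depend on this point.

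**Step 1: predictability.**

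- A block of 2 is either Supplement-first then Control-first, or the reverse. The second entry is fixed once the first is known. There are 30/2 = 15 blocks, so 15 of 30 orders (50%) are certain. This assumes that the first order of a pair is known when the second woman is enrolled, which an unconcealed allocation permits.
- Guessing the first of each pair at random and deducing the second gives 15 × 0.5 + 15 × 1 = 22.5 correct of 30, or 75%. Simple randomisation would give 50%.
- If the list itself is visible to recruiters, the first of each pair is known too, so 50% is a lower bound.

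**Step 2: what another block size would do.** For a block of 2m with m of each order, the expected number of fully determined entries is 2m/(m + 1). The expected number of correct guesses is m + [4^m / C(2m, m) − 1]/2.

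| Scheme | Certain in advance | Correct guesses |
|---|---|---|
| Blocks of 2 | 1/2 = 50% | 1.5/2 = 75% |
| Blocks of 4 | 1.33/4 = 33% | 2.83/4 = 71% |
| Blocks of 6 | 1.5/6 = 25% | 4.1/6 = 68% |
| One 15/15 permutation | 1.875/30 = 6% | 17.96/30 = 60% |

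Randomly mixed blocks of 4 and 6 gave about 69% correct guesses by simulation, and blocks of 2, 4 and 6 about 70%. Varying the block size alone therefore gains little. Concealment is the part that matters.

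**Step 3: how order can bias the contrast.** Let τ be the treatment effect and p the change from the first to the second session. The Supplement-minus-Control difference is τ − p for a Supplement-first woman and τ + p for a Control-first woman. Averaged over all complete pairs, ignoring the baseline covariate:

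bias = (n_CF × p_CF − n_SF × p_SF) / (n_CF + n_SF)

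where CF and SF denote Control-first and Supplement-first.

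- *15/15, same p in both orders:* (15p − 15p)/30 = 0. A common additive period effect cancels, even with no period term.
- *15/15, p differing between orders:* (p_CF − p_SF)/2. Steering can produce this, and a period term does not remove it.
- *Unequal orders, same p:* the fraction (n_CF − n_SF)/(n_CF + n_SF) of p enters the contrast. One-sided loss of 3 gives 15/12, so 3/27 = 11%. One-sided loss of 5 gives 15/10, so 5/25 = 20%.

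The two loss scenarios are assumptions, because the article states no dropout rate. They also assume that the models are run as described, without a period term.

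**The case against.** The strongest reply is that this is a crossover. Each woman is her own control, so steering fitter women or one contraceptive group to one order does not by itself shift the mean within-woman difference. Blocks of 2 also have a real benefit: they hold the orders at 15/15 if all thirty complete, which is what makes a common period effect cancel. Eligibility rests largely on measured cut-offs, the primary outcome is a laboratory isotope measure, and sessions are at least two weeks apart. All of this stands, and it limits the importance of the point. It does not remove the route through a differing learning or period effect, and the article gives no reason for forgoing concealment.

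A reader might go further in four ways that the documents do not support:

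- *That staff know every order before enrolment.* No section says when the order is generated or revealed relative to consent or eligibility. Full predictability is possible but not stated, and there is no evidence that steering would occur.
- *That a larger share of a period effect would leak through.* Thirty women in blocks of 2 gives at most 15 per order, and losses can only lower each count. With 27 completers the worst split is 15/12, or 11%.
- *That concealment would prevent order-related withdrawal.* In an open trial each woman knows her order by visit 2 in any case. The 11% and 20% figures depend on later loss and on the model, and concealment changes neither.
- *That the laboratories know the condition.* The article does not say so, and assay blinding is a separate matter from allocation.

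**Conclusion.** The point holds as a modest weakness in the design, not a numerical error. The stated scheme makes at least 15 of 30 orders predictable, with about 75% expected correct guesses, given one sequence and knowledge of the preceding order. The treatment contrast is biased only if the period or learning effect differs between the women channelled to each order, by half that difference at 15/15, or if the orders finish unequal. In the unequal case, 11% (15/12) or 20% (15/10) of a common period effect passes through under the assumed losses and the models as described. The documents give no estimate of any period effect, so the bias cannot be put in units of the outcome. The change is worth making because it is cheap and protects the claim of random order, not because the result is shown to be at risk.

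**What to change.** In Methods, delete the statement that allocation is not concealed and replace the fixed block of 2. Prepare the order list in advance, as one balanced 15/15 permutation or with randomly varying block sizes. Keep it from those who enrol and schedule, in sealed envelopes or a locked file. Release each order only after eligibility and consent are recorded and visit 2 is booked. Concealing the order does not require blinding, so the open design is no obstacle.

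**Cost.** A list and envelopes, or a locked file. Sample size, visits and treatment are unchanged. The downside is that the orders may be slightly unbalanced if recruitment stops early.

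**What it leaves open.** Withdrawal related to order after an open allocation is not addressed by this change.

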**Fig. 1 Fig1:**
[figure not shown]
Overview of the study design. Ca^2+^, calcium; Questionnaires: physical activity readiness questionnaire, menstrual history questionnaire, and Eating Attitudes Test – 26 item; Diaries: exercise and menstrual; DXA, dualenergy X-ray absorptiometry; $$\dot V$$O_2_max, maximal rate of oxygen uptake.

### Participants

Thirty women will complete this randomised controlled crossover trial. Participants will: be aged 18 to 36 years old; have a maximal rate of oxygen uptake ($$\dot V$$O_2max_) of ≥ 35 mL·kg^−1^·min^−1^; will be eumenorrhoeic or using the combined oral contraceptive pill, an intrauterine system, or intrauterine device; be weight stable, defined as no change in self-reported body mass ≥ 5% over the previous 3 months; have a BMI between 18 and 30 kg·m^−2^, and; not be pregnant or lactating. Women will be excluded if they: have disordered eating, defined as ≥ 20 on the Eating Attitudes Test – 26 item (EAT-26); are vitamin D deficient, defined as a total 25-hydroxyvitamin D (25(OH)D) < 30 nmol·L^−1^; have a total areal BMD T-score of < − 1; are oligomenorrhoeic or amenorrhoeic (< 9 menstrual cycles in previous 12 months); self-report as currently smoke or vape or have stopped smoking within the previous three months; are taking any medication known to affect bone or calcium metabolism (*e.g.* treatment for thyroid disorders); have a history of heart, liver, or kidney disease, diabetes, or thyroid disorder; have had a stress fracture or other bone injury in the previous 12 months, or; are anaemic (haemoglobin < 12 g·dL^−1^).

### Recruitment

Regular and Reserve military servicewomen, and female civilians, will be invited to volunteer. Individuals interested in particpating will contact the investigators, upon which they will recieve a Participant Information Sheet and be invited to a phone conversation. The study aims, requirements, right to withdraw, and risks will be outlined. This study has received favourable ethical opinion from the Ministry of Defence Research Ethics Committee (1021/MoDREC/19). During this study participants will therefore be covered by the Ministry of Defence for compensation under the provisions of the no-fault compensation scheme.

### Pre-screening

Consent to participate will be obtained from all volunteers by the investigators. Participants will have the option to consent for any remaining samples to be retained for follow-up analyses related to calcium metabolism, bone health, and endocrine function.

#### Height and body mass

Height will be measured using a stadiometer (Seca, UK) and body mass will be measured using calibrated weighing scales (Seca, UK) with participants wearing a T-shirt and shorts.

#### Questionnaires and activity monitoring

Participants will be asked to complete an adjusted physical activity readiness questionnaire [29], a menstrual history questionnaire [30], and the EAT-26 questionnaire [31, 32]. Participants will be asked to declare any current medication and dietary supplement use, including hormonal contraceptives, and previous history of stress fracture. Participants will be issued a menstrual diary to record down menses dates until the end of their participation in the study to aid scheduling of load carriage sessions. Habitual exercise energy expenditure (kcal) will be measured over seven days following the pre-screen visit from raw accelerometery data during periods of purposeful exercise recorded in an exercise diary [33]. Accelerometery data will be obtained from a wrist-worn device (GENEActiv, Activinsights, UK) worn for 24 h per day and sampled at 100 Hz [33]. Purposeful exercise will be defined as training/competition sessions, including leisure or transport activities (*e.g.* running, cycle to work, hiking, swimming, military physical training).

#### Blood sample

A single venous blood sample will be drawn into vacutainers from a vein in the antecubital fossa for the measurement of haemoglobin, serum total 25(OH)D for vitamin D status and intact PTH (iPTH) [29].

#### Dual-energy X-ray absorptiometry (DXA)

Participants will initially complete a pregnancy test to confirm they are not pregnant. A whole-body scan (Lunar iDXA™, GE Healthcare) will be performed with participants lying supine on the scanning table. Participants will be asked to wear shorts and a T-shirt and remove any jewellery. Whole-body and regional areal BMD, T-score, fat mass, fat-free mass, and lean mass will be determined from the scan.

#### Maximal rate of oxygen uptake

An incremental maximal exercise treadmill test (ELG, Woodway, USA) will be performed to determine $$\dot V$$O_2max_ [34]. Participants will run on the treadmill at a starting speed of 5 km·h^−1^ with the speed increased by 1 km·h^−1^ per minute until volitional exhaustion. Expired gases (Metalyzer 3B, Cortex, Germany) and heart rate (H10, Polar, Finland) will be measured continuously. Maximal rate of oxygen uptake will be taken as the highest 30 s average $$\dot V$$O_2_. Where $$\dot V$$O_2max_ criteria is not attained (34) $$\dot V$$O_2peak_ will be reported.

### Load carriage 1 and 2

Participants who meet the inclusion criteria from pre-screening will complete two independent load carriage exercise sessions in the laboratory separated by a minimum of two weeks. Participants not taking any hormonal contraceptives will track their menstrual cycle with the provided menstrual diary and start each experimental testing session in the late lutal phase/early follicular phase (within the few days just before or after menstruation). Participants using the combined oral contraceptive pill will complete each experimental testing session during the seven day break between pill packets; participants taking back-to-back combined oral contraceptive pill packets, using an intrauterine system, or intrauterine device will be tested at any point.

In the 24 h preceding each load carriage session participants will be rested (no exhaustive exercise) and will not apply skin moisturizer. Participants will arrive at the laboratory after an overnight fast, have an indwelling cannula inserted in a vein in the antecubital fossa, and a resting blood sample taken (Fig. 2). A calcium supplement (2 × 500 mg; Calcichew) will be given to each participant completing the Supplement condition ~ 60 min before starting the load carriage exercise [8]. Sweat collectors (Macroduct Sweat Collector, ELITech Group, France) [35] will be attached to the forearm for the measurement of sweat calcium excretion during exericse. A 120 min session of load carriage exercise will be completed. The load carriage exercise is a fitness test completed by the infantry. Participants will walk 12.8 km on the treadmill at 6.4 km·h^− 1^ for 120 min whilst wearing a 20 kg military backpack. Expired gases, heart rate, and rating of perceived exertion will be measured throughout the exercise. The first urine void upon waking (Fig. 2), and a urine void within ~ 1 h of the cessation of load carriage, will be obtained for the measurement of calcium isotopes for the calculation of bone calcium balance. Nude body mass will be measured before and immediately after exercise for the determination of sweat loss and calculation of sweat calcium excretion; post-exercise body mass will be adjusted for water consumed *ad libitum* during exercise. Calcium concentration of water consumed during exercise will be recorded. Blood samples will be taken at 0 min, and then every 20 min during, and 15, 30, 60, and 90 min following, load carriage. Blood samples fractioned into serum and plasma will be analysed for markers of bone formation, bone resorption, and calcium metabolism. Whole blood will be analysed immediately for blood lactate concentration (Lactate Pro 2, Arkray, Japan), ionized calcium, haemoglobin and haematocrit (i-STAT Alinity, Abbott, USA; CHEM8^+^, Abbott, USA) (Fig. 2). Isokinetic (60°·s^− 1^ and 180°·s^− 1^) and isometric (90° knee flexion) maximal voluntary contraction of the knee extensors and flexors (System 4, Biodex Medical Systems, USA) will be measured before and immediately after load carriage exercise. Researchers will monitor the laboratory testing procedures to ensure adhereance to study protocols; there is no criteria for the study to be discontinued.

